### Interventions

The test group (TG) will consist of intensive periodontal treatment comprising one session of supragingival scaling and personalized oral hygiene instructions, followed by one to four sessions of subgingival scaling and root planing (SRP) by quadrant, under local anesthesia, in a period of 14 days. Individuals will be followed monthly during the first 6 months and at each 3 months until the end of the 12-month study period. In the follow-up sessions, professional plaque removal, oral hygiene instructions and reinforcement will be provided.

The control group (CG) will receive community periodontal treatment similar to that provided by the Brazilian public health system, consisting of only one session of supragingival scaling followed by standard oral hygiene instructions.

Treatments will be performed by two experienced periodontists ([name] and [name]). Before the beginning of the study, the two clinicians will undergo a period of training and discussion of the therapeutic approaches with the aim of standardization of the test and control interventions.

### Study protocol

Eligible individuals will be invited to follow the protocol of visits described below (Figure 1):

**Figure 1 F1:**
[figure not shown]
Flowchart of the study participation and examinations.

•Visit I: application of a structured questionnaire, general clinical evaluation, baseline periodontal examination and subgingival microbiological samples.

•Visit II: baseline flow-mediated dilation, anthropometric assessment and blood samples.

•Visit III: Start of periodontal treatment according to randomization. After this visit, periodontal therapy will be conducted according to randomization.

•Visit IV (30 days after the last session of periodontal treatment): first follow-up flow-mediated dilation assessment.

•Visit V (3 months after the last session of periodontal treatment): second follow-up flow-mediated dilation assessment, first follow-up blood samples, periodontal clinical examination and subgingival microbiological samples.

•Visit VI (6 months after the last session of periodontal treatment): third follow-up flow-mediated dilation assessment, second follow-up blood samples and periodontal clinical examination and subgingival microbiological samples.

•Visit VII (12 months after the last session of periodontal treatment): final follow-up blood samples, periodontal clinical examination and subgingival microbiological samples.

### Randomization

Stratified randomization will be conducted. Individuals will be stratified into localized or generalized periodontitis groups using a cutoff point of 30% of teeth with clinical attachment loss ≥ 6 mm since the extent of disease may be a prognostic factor for the response to non-surgical periodontal treatment.

A specific program (randomization.com) for allocation in test and control groups will be used by generating a random numbers sequence. Randomization will be conducted in blocks of 20 individuals after attributing codes to each participant. An external assistant not involved in the study will conduct randomization to warrant allocation concealment. Codes will be kept until the end of analyses to maintain blindness of the examiner and statistician.

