### Sample size

The sample size of the present trial was estimated using a statistical software (G*Power 3 for Macintosh). The change in serum levels of C-reactive protein was considered the main outcome for sample size estimation. It was estimated that 42 individuals in each treatment arm will be necessary to find reductions in C-reactive protein of 1.5 mg/l (standard deviation = 1.5) and 0.5 mg/l (standard deviation = 0.5) in the test and control groups, respectively. Alpha and beta errors of 5% and 20%, respectively, were used in the estimation. An attrition rate of 20% is expected during the study; consequently, 50 patients in each group will be included.

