### Primary outcome

The primary outcome of the present trial will be changes in serum concentrations of C-reactive protein.

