### Independent/exposure variables and confounding

The main exposure variable will be composed by test and control periodontal treatments. The impact of each treatment on the primary and secondary outcomes will be evaluated controlling for the following confounding factors: age, gender, BMI, physical activity, glycated hemoglobin, use of oral hypoglycemic drugs, smoking exposure and subgingival microbiota.

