### Statistical analyses

Continuous variables will be described using means and standard deviations or median and range in case of asymmetric distribution of data. Categorical variables will be presented using frequency distribution. An intention-to-treat approach will be used in the analysis of this trial taking into consideration all dropouts during the follow-up period.

Univariate analyses will be conducted using chi-square and *t* tests for independent samples. Multivariate models will be fitted using generalized estimating equations to compare changes in each outcome according to test and control periodontal treatment groups controlling for confounding factors. *P* values <0.05 will be considered statistically significant. A statistical package (Stata 12 for Macintosh, STATA Corp., College Station, TX, USA) will be used. The individual will be considered the unit of analysis.

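### Randomisation is stratified by localized versus generalized periodontitis, but the stated analysis omits that stratum, so reported standard errors are conservative to whatever extent the stratum predicts CRP change

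*Protocol article*

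**What the plan says.** All references are to the protocol article.

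- Randomization: "Individuals will be stratified into localized or generalized periodontitis groups using a cutoff point of 30% of teeth", the criterion being attachment loss of at least 6 mm. The reason given is "since the extent of disease may be a prognostic factor for the response to non-surgical periodontal treatment". Allocation is blocked: "Randomization will be conducted in blocks of 20 individuals after attributing codes to each participant".
- Independent/exposure variables and confounding: the effect of treatment on the primary and secondary outcomes is to be evaluated controlling for "age, gender, BMI, physical activity, glycated hemoglobin, use of oral hypoglycemic drugs, smoking exposure and subgingival microbiota". Neither the stratum nor any other measure of periodontitis extent is among the eight.
- Statistical analyses: "Univariate analyses will be conducted using chi-square and *t* tests for independent samples". Then: "Multivariate models will be fitted using generalized estimating equations to compare changes in each outcome according to test and control periodontal treatment groups". Those models adjust for confounders, which can only mean the eight just named.
- Primary outcome: "The primary outcome of the present trial will be changes in serum concentrations of C-reactive protein".

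No other section carries the stratum into an analysis.

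**The concern.** Blocking within strata holds the arms nearly balanced on the stratum. Between-stratum variation in the outcome therefore largely drops out of the sampling variance of the treatment difference. A model without the stratum still counts that variation as residual noise and reports a standard error for a trial that was not stratified. If the stratum is prognostic for the outcome, the reported standard error exceeds the true one, the test rejects less often than 5% under the null, and intervals are wider than they need be. The usual robust GEE standard errors do not cure this, because they also treat allocation as unstratified.

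The article does not leave covariates to a later document. It writes out a list, and the variable chosen for balance by design is not on it.

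**Working it through.** **The plan's own figure.** The Sample size section gives mean CRP reductions of 1.5 mg/l (SD 1.5) and 0.5 mg/l (SD 0.5), alpha 5%, power 80% and 42 per arm.

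- Root-mean-square SD = √((1.5² + 0.5²)/2) = √1.25 = 1.118.
- n per arm = 2 × (1.96 + 0.8416)² × 1.25 / 1.0² = 19.6, so 20 by the normal formula; a t test gives 21.

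The stated 42 per arm does not reproduce from these inputs. That is a separate matter. Here it means only that power at 42 per arm is well above 80%.

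**Inputs for this point.** Let R² be the share of variance in CRP change that the stratum explains: partial R² given the eight covariates for the GEE model, simple R² for the t test. The documents give no value. I assume 0, 5, 10 and 20%.

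**Formulas.** Scale the reported standard error without the stratum to 1. Under stratified allocation the true standard error is √(1 − R²).

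- Overstatement of the standard error = 1/√(1 − R²).
- True type I error = 2 × [1 − Φ(1.96/√(1 − R²))].
- With λ = difference/reported standard error: power without the stratum = Φ((λ − 1.96)/√(1 − R²)); power with it = Φ(λ/√(1 − R²) − 1.96).

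For 42 per arm and a difference of 1.0 mg/l:

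- SD 1.118: standard error = 1.118 × √(2/42) = 0.244, λ = 4.10.
- SD 1.5 in both arms (a pessimistic assumption, not the protocol's): standard error = 0.327, λ = 3.06.

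A test with nominal power of 80% has λ = 2.80.

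| Assumed R² | SE too large by | True type I error | Power, SD 1.118: without / with stratum | Power, SD 1.5: without / with | Power, λ = 2.80: without / with |
|---|---|---|---|---|---|
| 0 | 0% | 5.0% | 98.4 / 98.4% | 86.3 / 86.3% | 80 / 80% |
| 5% | 2.6% | 4.4% | 98.6 / 98.8% | 86.9 / 88.0% | 81 / 82% |
| 10% | 5.4% | 3.9% | 98.8 / 99.1% | 87.6 / 89.6% | 81 / 84% |
| 20% | 11.8% | 2.8% | 99.2 / 99.6% | 89.0 / 92.7% | 83 / 88% |

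In each power pair the first figure rises with R². That is the retained benefit of stratified allocation, present even when the analysis ignores the stratum.

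**Simulation check.** 100 patients, two strata equally likely, permuted blocks of 20 in each stratum (last blocks may be part-filled), no treatment effect, a linear model with and without the stratum, 6,000 runs per R².

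- Type I error without the stratum, for R² = 0, 5, 10, 20%: 5.1, 4.7, 4.1, 2.9%. With it: about 5% throughout.
- At R² = 20%, the mean reported standard error was 0.200 without the stratum and 0.178 with it; the true sampling SD of the unadjusted estimate was 0.181.

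This agrees with the formulas within simulation error (about 0.3 percentage points).

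**How plausible is the range?** With equal strata and total SD 1.118, R² corresponds to a between-stratum gap in CRP change of 2 × √R² × 1.118 mg/l: 0.5, 0.7 and 1.0 mg/l for 5, 10 and 20%. The 20% case needs the two strata to differ by as much as the whole treatment effect assumed for the trial, which is 1.5 − 0.5 = 1.0 mg/l. It is best read as an upper end.

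**The case against.** The strongest objection is that the harm depends on something the protocol never asserts. The Randomization section says only that extent may be prognostic, and for the response to periodontal treatment; it does not mention CRP, lipids or flow-mediated dilation. If extent does not predict CRP change, R² is zero and the standard errors are right. This stands, and it is why zero belongs in the range. The trial's premise is that periodontal treatment acts on CRP, so a predictor of periodontal response could plausibly predict CRP change, but that is an inference.

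Second, the GEE model already holds eight covariates, and what matters is what the stratum adds to them. Any overlap shrinks the effect, and subgingival microbiota may be a partial proxy. This stands too, with the limit that three species sampled at the four deepest sites do not measure the proportion of teeth affected. The t tests have no covariates at all.

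Third, the list is headed as confounding factors, and a factor balanced by design is not a confounder, so its absence need not be a deliberate exclusion; fuller model terms may sit in a document not shown. This carries some weight, but the list is explicit and is said to govern the primary and secondary outcomes.

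A reader might also infer more than the documents support:

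- That the gain from stratifying is lost. It is not: balance and the lower true variance remain, and power without the stratum still rises with R². What is missing is their full reflection in the reported standard errors, intervals and p values.
- That the result is biased or false positives are inflated. Neither follows; the error is conservative.
- That part-filled blocks of 20 will leave the arms unbalanced within strata. They can, but stratum sizes are not given, and in the simulation they raised the true sampling SD only slightly (0.181 against a reported 0.178 with adjustment, at R² = 20%).

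**Conclusion.** The omission is certain: the design stratifies on periodontitis extent and no stated analysis includes it. The direction is also clear. To the extent that the stratum predicts CRP change beyond the eight listed covariates, reported standard errors and intervals are conservative and some precision is forgone.

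The size is not in the documents. Across the assumed range it runs from nothing to standard errors about 12% too large and a type I error of about 2.8%. At 42 per arm the power forgone is at most about 0.4 percentage points on the protocol's own SDs, and about 4 points if the SD were 1.5 in both arms. The figures rest on a linear model for change, near-balance within strata and the assumed R².

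This is an inexpensive improvement that should be made. It does not threaten the validity of the primary comparison.

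**What to change.** Add the randomisation stratum (localized or generalized at the 30% cutoff, as recorded at randomisation) as a fixed covariate in every model that estimates a treatment effect, including the primary GEE model for CRP. Say so both in the covariate list and in the Statistical analyses section, and describe the stratum as a design factor so that its place does not depend on whether it counts as a confounder. Take treatment-effect inference from these models and not from the unstratified t tests.

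The cost is one degree of freedom among 100 patients. No new data are needed, because the stratum must be known before allocation. The article describes recruitment as ongoing, so at that stage the change could be made before any unblinded analysis.

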### Blood markers

Each individual will provide two 10-ml samples of blood collected by a trained nurse from the antecubital fossa. Fasting blood samples will be obtained between 7:00 a.m. and 12:00 p.m. to control for possible diurnal variations. Blood samples for traditional cardiovascular blood markers will be immediately centrifuged and analyzed. Blood samples used for proinflammatory and endothelial markers will be centrifuged at 4°C and 4.000 rpm for 10 min (ALC PK 120 R, ALC International, Milan, Italy). The serum will be sampled and stored in Eppendorf tubes at −80°C until analysis.

Traditional cardiovascular blood risk markers to be assessed will be glucose, glycated hemoglobin, triglycerides (TG), total cholesterol, and high- and low-density lipoprotein cholesterol (HDL-C and LDL-C). The following proinflammatory markers will be assessed: C-reactive protein, interleukin 1β (IL-1β), IL-6, tumor necrosis factor α (TNFα) and fibrinogen. ICAM-1, VCAM-1 and E-selectin will be the measured to assess the endothelial function. These markers will be measured at baseline, 3, 6 and 12 months after treatment.

High-sensitive CRP, glucose, TG, total cholesterol and HDL-C will be measured by automated enzymatic colorimetric methods (ADVIA 1800, Siemens, Germany) following the manufacturer’s instructions. CRP will be measured using the intensified immunoturbidimetry by latex (CRP_2). Glucose will be obtained using the glucose-hexokinase method II (GLUH). Total cholesterol will be dosed by the colorimetric enzymatic method (CHOL_2) with cholesterol-esterase and cholesterol oxidase followed by a Trinder type endpoint. Triglycerides will be measured by the Trinder GPO method. HDL-C will be assessed by the HDL-*Directo* (HDL-D) using the principles of elimination/catalase. LDL-C will be calculated using the Friedwald formula [LDL-C = total cholesterol – (HDL-C + TG/5)]. Non-HDL-C will be calculated by the subtraction of HDL-C from total cholesterol. Very low density lipoprotein cholesterol (VLDL-C) will be calculated dividing TG by 5. Glycated hemoglobin will be obtained by high-precision chromatography (Merck-Hitachi L-9100, Merck, Germany).

Proinflammatory and endothelial function blood markers will be measured using specific kits for Luminex (Milliplex map human panels, EMD Millipore Corp., Billerica, MA, USA).

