**Methods/design:**

This is a randomized, parallel design, examiner blinded, controlled clinical trial. Individuals from both genders, 35 years of age and older, with concomitant diagnosis of CAD and periodontitis will be included. CAD will be defined as the occurrence of at least one of the following events 6 months prior to entering the trial: documented history of myocardial infarction; surgical or percutaneous myocardial revascularization and lesion >50% in at least one coronary artery assessed by angiography; presence of angina and positive noninvasive testing of ischemia. Diagnosis of periodontitis will be defined using the CDC-AAP case definition (≥2 interproximal sites with clinical attachment loss ≥6 mm and ≥1 interproximal site with probing depth ≥5 mm). Individuals will have to present at least ten teeth present to be included. One hundred individuals will be allocated to test (intensive periodontal treatment comprised by scaling and root planing) or control (community periodontal treatment consisting of one session of supragingival plaque removal only) treatment groups. Full-mouth six sites per tooth periodontal examinations and subgingival biofilm samples will be conducted at baseline, 3, 6 and 12 months after treatment. The primary outcome of this study will be C-reactive protein changes over time. Secondary outcomes include levels of total cholesterol, LDL-C, HDL-C, triglycerides, IL-1β, IL-6, TNFα, fibrinogen, ICAM-1, VCAM-1 and E-selectin. These outcomes will be assessed at all time points over 12 months. Flow-mediated dilation will be assessed at baseline, 1, 3 and 6 months after periodontal therapy.

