### Secondary outcomes

Secondary outcomes will include:

•Non-invasive measurements of endothelial function (FMD);

•Traditional cardiovascular risk markers (total cholesterol, LDL-C, HDL-C and triglycerides);

•Proinflammatory biomarkers (IL-1β, IL-6, TNFα and fibrinogen);

•Endothelial function biomarkers (ICAM-1, VCAM-1 and E-selectin).

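### As written, fibrinogen, one of 12 secondary outcomes, would be measured in stored serum, from which clotting has removed most of it; the specimen must be confirmed and the text or the tube corrected

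*Protocol article*

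**What the plan says.** Fibrinogen is a declared outcome. The Secondary outcomes section lists "Proinflammatory biomarkers (IL-1β, IL-6, TNFα and fibrinogen" as one group, and the abstract's Methods/design paragraph includes it as well.

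The Blood markers section puts it in the same class: "The following proinflammatory markers will be assessed: C-reactive protein, interleukin 1β (IL-1β), IL-6, tumor necrosis factor α (TNFα) and fibrinogen". The handling of samples for that class follows: "Blood samples used for proinflammatory and endothelial markers will be centrifuged at 4°C and 4.000 rpm for 10 min", and then "The serum will be sampled and stored in Eppendorf tubes" at −80 °C until analysis. The assay is also given by class: "Proinflammatory and endothelial function blood markers will be measured using specific kits for Luminex". The visits for these markers are baseline, 3, 6 and 12 months.

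The statement of aim, both in the abstract and at the end of the Background section, likewise refers to serum concentrations for the proinflammatory and endothelial markers.

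**The concern.** Serum and plasma are not interchangeable for this analyte. Serum is by definition the fluid left once blood has clotted. Clotting converts fibrinogen to fibrin, and the fibrin goes with the clot. What can still be read in serum is residue, and its amount depends on how complete the clotting was, not on how much fibrinogen was circulating. Neither randomisation nor a larger sample restores an analyte that the specimen no longer holds in proportion to the blood level.

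Fibrinogen also belongs to the trial's rationale. The Background section counts it among the molecules in the cardiovascular cascade and among the markers raised in periodontitis, and it cites a study in hypertensive patients in which periodontal therapy might reduce it. A null result from serum would look like a failure to confirm that signal, although the quantity of interest had not been measured.

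**Working it through.** The plan gives no figure for this point, so the check traces one analyte through the text and then counts what depends on it.

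**Tracing fibrinogen**

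1. Outcome status: secondary outcome (abstract; Secondary outcomes).
2. Marker class: proinflammatory, with CRP, IL-1β, IL-6 and TNFα (Blood markers).
3. Processing of that class: centrifuged at 4 °C for 10 minutes, serum kept at −80 °C (Blood markers).
4. Assay of that class: Luminex kits (Blood markers).
5. Exceptions: CRP is given its own immunoturbidimetric assay on the automated analyser. No exception is given for fibrinogen.
6. Search for an alternative: no section of the article mentions plasma, citrate, EDTA, any other anticoagulant or a separate fibrinogen method.

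Steps 2 to 5 lead to a single reading of the text: fibrinogen is measured in stored serum.

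**How much of the outcome set is concerned**

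The Secondary outcomes section contains flow-mediated dilation (1), total cholesterol, LDL-C, HDL-C and triglycerides (4), IL-1β, IL-6, TNFα and fibrinogen (4), and ICAM-1, VCAM-1 and E-selectin (3). That is 1 + 4 + 4 + 3 = 12, so fibrinogen is 1 of 12. The argument does not reach CRP or the other 11.

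**How many determinations, if serum really is used**

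- Inputs: 50 patients per group, hence 100, and 20% expected attrition (Sample size); four blood visits (Blood markers; Study protocol).
- Ceiling: 100 × 4 = 400.
- With 20% attrition, 80 patients complete. If all losses fall between baseline and month 3: 100 + 80 + 80 + 80 = 340. If all fall between months 6 and 12: 100 + 100 + 100 + 80 = 380. The timing of dropout is not stated, so the range is 340 to 380.

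**How many baselines may already be affected**

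Baseline blood is taken at Visit II and treatment starts at Visit III (Study protocol). Blocks hold 20 patients (Randomization), and a first block is under treatment (Trial status). So about 20 of 100 patients have had baseline blood drawn and would lack a valid fibrinogen baseline if only serum was kept. Patients enrolled after that block could still be sampled correctly.

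**The case against.** The best case against the point is that the article is condensed and *serum* may be loose wording.

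- No sentence says outright that fibrinogen is measured in serum. The link runs through class-level statements, and the Luminex statement is not literally true of its whole class, because CRP is measured elsewhere. This weakens the inference but does not remove it: the departure for CRP is spelled out, and none is spelled out for fibrinogen.
- Tube types are not given for any marker. Glycated hemoglobin, also on the list, is a red-cell measure that needs unclotted blood, so an anticoagulated sample is probably drawn without being mentioned. The absence of a described plasma tube therefore proves little, and such detail may sit in the full protocol. This stands. The point rests on the word *serum*, which is stated and repeated in the aim, not on what is left out.
- No clotting step is described, so plasma may have been meant. This also stands as a possibility. The text would then still be wrong, but no data would be lost.
- Handling is the same in both arms, so the main risk is loss of sensitivity in one secondary outcome, not a bias in the trial's conclusion. This stands.

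A reader might go further and infer that the fibrinogen data are certainly worthless and that the first block's baselines are already beyond recovery. The documents do not support that. They do not say which tubes were drawn, give no data on residual fibrinogen, and do not show whether usable plasma was kept for those patients.

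**Conclusion.** The point holds for the text as it stands. Following the Blood markers section would put a named secondary outcome on a specimen that cannot validly reflect it, and a null fibrinogen result would be uninterpretable. The conclusion rests on the general definition of serum and on reading the class statements as covering fibrinogen.

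The loss is conditional on serum actually having been used. In that case it is at most 400 determinations before attrition (340 to 380 with the expected dropout, depending on its timing) and possibly about 20 baselines. If the tube was anticoagulated, the defect is a wrong word. In both cases the plan needs a correction before further blocks are sampled.

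**What to change.** First confirm which tube and which specimen are used for fibrinogen.

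- **If the tube is anticoagulated:** correct *serum* to *plasma* for fibrinogen in the Blood markers section, and adjust the statement of aim to match. No data are affected.
- **If it is truly serum:** collect an anticoagulated aliquot at the same venepuncture and measure fibrinogen in plasma, with an assay suited to plasma, at baseline, 3, 6 and 12 months. State in advance that fibrinogen is treated as missing at any visit sampled only in serum.
- **If plasma cannot be collected:** remove fibrinogen from the secondary outcomes.

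The first option costs a small text edit. The second costs a different tube or aliquot at a draw that already takes place, a check that the two 10-ml samples still cover the other assays, and possibly a missing baseline fibrinogen for about one block of 20 patients. The third gives up one of 12 secondary outcomes.
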